#### Smoking Cessation Interventions for all Patients

All participants have identical treatment to stop smoking. This is the treatment which is available on the NHS. It is withdrawal orientated such that behavioural strategies and nicotine replacement are given to relieve withdrawal symptoms. This has been shown to be an effective model for stopping smoking [29]. Individuals are seen over 7 consecutive weeks, weeks -3 and -2 prepare them for quitting, they quit at week 0, weeks +1, +2, +3 and +4 support them during the first 4 weeks after quitting when withdrawal symptoms are at their strongest. The sessions incorporate a variety of behavioural change techniques, pre-quit sessions prompt intent formation (technique 4) by setting a quit date, they prompt barrier identification (technique 5) and relapse prevention (technique 23) when participants identify times or places when it will be particular hard for them to resist smoking, they discuss a strategy to help them to deal with these circumstances; for example, changing routine so the usual smoking cues are removed. Quit week and the weeks that follow provide instruction (technique 8) in the use of nicotine replacement, review of and further planning of strategies (technique 11) to deal with withdrawal symptoms and general encouragement (technique 6). Self-talk (technique 22) is encouraged such that participants are asked to see and describe themselves as a 'non-smoker' and to frequently bring to mind the benefits of quitting that they are looking forward to.

##### Nicotine replacement therapy (NRT)

Nicorette 25 mg transdermal 16 hour patches are provided for 8 weeks followed by a 15 mg patch and a 10 mg patch each for 2 weeks. Patches are supplied free of charge by McNeil Products Ltd. Other forms of NRT, such as gum or nasal spray or a combination of NRT is not used to avoid the possibility that the amount of NRT taken would differ by arm. This could confound effects of hunger or ketosis on urges to smoke that we are trying to discover. We are using a nicotine patch as it delivers a consistent amount of nicotine to avoid this confounding. As no other NRT products can be used in combination to help with acute cravings we are using the 16 hour, 25 mg patch which has been shown to yield better abstinence than other available patches [30].

#### Training and supervision

Treatment is provided by trained practice nurses. Training is given by NHS stop smoking services (2 days), a research nurse and a general practitioner (GP) (1/2 day), and a registered dietitian (1.5 days). Nurses are given the clinical protocol to read before training sessions. Training includes explanation of dietetic and behavioural interventions and practicing the interventions on each other. The clinical protocol is clarified where needed and questions answered. The aim of the training is to equip the nurses so that, once they have completed it, they feel confident to deliver the interventions according to the clinical protocol.

After the training, 'hands on' supervision is available for the first few clinics. Immediate telephone access to the dietitian and GP is available for all clinical queries throughout the rest of the trial.

Medical history and any medication used or altered during the trial is monitored. Any significant changes in clinical condition of individual participants, as measured on a weekly basis, is discussed with the supervising GP and action taken, e.g. clinically significant fall in blood pressure in participants on the VLCD taking anti-hypertensives will require adjustment of anti-hypertensive medication. The participant's own GP is kept informed.

#### Fidelity checking and monitoring

Fidelity to the clinical protocol and record keeping is assessed and monitored against the clinical protocol by the principal investigator every few months; consultations are audiotaped for this purpose. Any deviations are recorded, discussed and corrected either immediately or at following clinics. The trial is potentially subject to audit by the appropriate regulatory authorities and therefore participants are asked to consent to allow their records to be viewed.

### Objectives

#### Primary objectives

To investigate the feasibility of running this three-armed dietary intervention as part of the NHS stop smoking services using primary care nurses,. This includes the feasibility of measuring and monitoring of physiological and biochemical risk factors for cardiovascular disease, diabetes and chronic obstructive pulmonary disease (COPD). It explores the acceptability of the interventions to participants.

#### Secondary objectives

To investigate whether smoking cessation advice and a nicotine patch in combination with: a very low calorie diet (VLCD), or individually tailored dietary planning (IDAP), or usual support affects urges to smoke, through hunger or ketosis in overweight smokers trying to quit.

#### Tertiary objectives

To investigate the extent to which changes in smoking status, diet and activity achieved during the treatment stages are maintained at the end of treatment and at 6 and 12 months in each of the intervention arms. To investigate associations between hunger, abstinence, early and late weight gain.

### Outcome Measures

#### Acceptability

Participant acceptability is measured qualitatively by semi-structured interviewing and quantitatively by response and attrition rates as described below:

• Semi-structured telephone interviews are conducted after the participant has completed or dropped out of the trial. Participants who are happy to do so will give their consent to this at the start of the trial. To help them remember their thoughts and feelings 'of the moment' they are given the questions they will be asked at the start of the trial, with space to jot down notes, during the trial. The number of participants being interviewed will continue until theoretical saturation of responses has been reached. We will purposively sample interviewees to encompass the full range of attrition characteristics, for example, those who completed the trial, and those who dropped out of quitting, dieting or both in each of the three trial arms. Interviews will be audio recorded and transcribed verbatim. Participants will be asked what they found helpful and unhelpful and their reasons for dropping.

• Rates of response to participant invitation letters and posters.

• Rates of recruitment at telephone screening, at first consultation.

• Rates of drop out before randomisation.

• Rates of drop out after randomisation in each treatment arm.

• Rates of attendance at each session.

• Rates of participant adherence to treatment.

• Quality of life measure, a scale on which the participant can score general life satisfaction and well being at baseline, weeks +4, and +12.

#### Feasibility

Feasibility of running the trial within the primary care practice will be measured qualitatively as described below:

• A focus group of participating clinicians to investigate experiences of delivering intervention, e.g. how easy was it to carry out the interventions, was training sufficient, was consultation time adequate, what difficulties were encountered taking the trial measurements.

• Principal investigator's reflections on their experiences of primary care involvement e.g. ease of GP practice recruitment, willingness for PCTs to participant, obstacles encountered.

#### Cost

The financial cost of running the trial will be calculated.

#### Measurement of urges to smoke and hunger

Degree of smoking addiction is measured at baseline using the Fagerstrom Score [31]. Urge to smoke is measured by the Mood & Physical Symptoms Combined Scale (MPSS-C) [32]. Hunger and food craving is measured by the Hunger and food Craving (HCS) score. MPSS-C and HCS are recorded daily in a dairy over the first four weeks of quitting and weekly thereafter. The primary outcomes of interest will be over the first 24 hours and the first week of quitting; this is where the largest effects are likely to be seen as withdrawal symptoms are at their peak during this time. Comparisons between measures are made for all those who continued in their quit attempt until they decided to abandon quitting, and adjusted for those who lapsed, were point prevalent abstinent at 24 hours, 7days or continuously abstinent at 4 weeks. Although it is standard practice in smoking trials to primarily analyse those who are abstinent, our interest is in the effects on cravings and we cannot assume that those who did not achieve abstinence did not experience cravings as they tried to do so. Piasecki showed that cravings were heightened in both smokers who were attempting to quit and lapsed as well as in smokers who succeeded in quitting. He found that more cigarettes, smoked on more occasions did reduced cravings (presumably as these have served to treat nicotine withdrawal acutely) but also that a few cigarettes increased cravings (100 vs 56 cigarettes p < 0.001) [33]. Perhaps this reflects a greater struggle to cope with cravings before a cigarette was finally smoked out of desperation.

#### Ketosis

The presence or absence of ketones will be measured using ketostik test strips dipped into urine samples. This will be done weekly during the first 6 weeks of dietary intervention, this is to check those in the VLCD are in ketosis throughout the five weeks and come out of ketosis during the re-feeding week. It is also measured during this time in IDAP and control arms to verify the absence of ketosis in these groups or identify any participants which might be self-imposing excessive dietary restriction, (unless undiagnosed diabetes presents itself).

#### Measurement of smoking status

Twenty-four hour point prevalence abstinence is measured by participants achieving 24 consecutive hours of abstinence as verified by exhaled CO < 10 ppm. Seven day point prevalence abstinence is defined as those not smoking over the last 7 days as verified by exhaled CO < 10 ppm. Participants achieving 1, 6 and 12 month abstinence as defined using the Russell Standard which states that no more than 5 cigarettes since have been smoked since week +2, this is verified by CO < 10 ppm at each consultation [34]. Participants who have not achieved abstinence but are still attempting to quit are termed 'lapsed'. Smokers who abandon their quit attempt, such that it is no longer their intention to quit, are considered 'relapsed'.

#### Measurement of Disease Risk Factors

These are measured as described below. The schedule of measurements is contained in table 2.

**Table 2 T2:** Measurements to be taken at each point in trial

Treatment week	-2	-1	0	1	2	3	4	5-7	8-10		12	26	52
Baseline Questionnaire (with Fagerstrom Score) 7 day food diary		√											

Weight		√	√	√	√	√	√	√	√	√	√	√	√

Waist/Hip ratio		√	√	√	√	√	√	√	√	√	√	√	√

BP/HR		√	√	√	√	√	√	√	√	√	√	√	√

Smoking Status		√	√	√	√	√	√	√	√	√	√	√	√

Urinary ketones		√	√	√	√	√	√						

Fasting Blood test	√										√	√	√

Lung function	√										√	√	√

Russell Standard									√		√	√	√

QOL measure		√					√				√		

Confidence in trial arm	√						√				√		

Percentage Body Fat composition		√	√	√	√	√	√	√	√	√	√	√	√

Daily Diaries		√	√	√	√	√	√						

Weekly Diaries								√	√	√	√	√	√

HCI		√									√	√	√

1. Weekly weight, waist to hip ratio, % body fat composition, blood pressure, and heart rate.

2. FEV1 and FVC post 200 mg salbutamol as is recommended by the American Thoracic Society 2005 standards for measuring lung function [35] at baseline, 3, 6 and 12 months.

3. Fasting blood glucose, Total cholesterol (TC), low density lipoprotein (LDL) cholesterol, high density lipoprotein (HDL) cholesterol TC/HDL ratio, triglycerides, haemoglobin, white blood cell count, platelet count, mean cell volume and c-reactive protein (CRP).

Full details of how these measurements are taken are contained within the trial clinical protocol as standard operating procedures (SOPs) and work instructions (WIs). The nurses are trained in these procedures so that they are carried out consistently at each trial site. The nurses are assessed in practice against these SOPs and WIs, every couple of months, by the principal investigator.

#### Measurement of diet and activity

Food choices, eating behaviour and activity are measured at baseline, end of treatment, 6 and 12 months using the HCI. Agreement between this simple, quick measure of diet quality will be assessed by statistical analysis against a detailed seven day food intake diary which is also completed at baseline. Participants are encouraged to weigh their food when completing the seven day food diary. Despite under-reporting in obese individuals, a 7 day weighed intake diary has been shown to be the most accurate measure of dietary intake [36]. Diaries which report less than 1.2 × BMR energy intake or are incomplete are discounted. If necessary the Goldberg cut-off can be used to evaluate the mean population bias in reported energy intake [37]. The seven day diaries also measure physically activity levels using the method which determined dietary references values for energy in the UK.

Those on a VLCD who do not produce ketones or achieve the expected 2 kg weekly weight loss will be considered non adherent. We would expect any weight gain in the IDAP group to be a result of poor adherence, although weight maintenance is acceptable in this group.

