**Methods:**

This is a 3 armed, unblinded, randomized controlled trial in overweight (BMI > 25 kg/m^2^), daily smokers (CO > 10 ppm); with at least 30 participants in each group. Each group receives identical behavioural support and NRT patches (25 mg(8 weeks),15 mg(2 weeks),10 mg(2 weeks)). The VLCD group receive a 429-559 kcal/day liquid formula beginning 1 week before quitting and continuing for 4 weeks afterwards. The modest energy restricted group (termed individual dietary and activity planning(IDAP)) engage in goal-setting and receive an energy prescription based on individual basal metabolic rate(BMR) aiming for daily reduction of 600 kcal. The control group receive usual dietary advice that accompanies smoking cessation i.e. avoiding feeling hungry but eating healthy snacks. After this, the VLCD participants receive IDAP to provide support for changing eating habits in the longer term; the IDAP group continues receiving this support. The control group receive IDAP 8 weeks after quitting. This allows us to compare IDAP following a successful quit attempt with dieting concurrently during quitting. It also aims to prevent attrition in the unblinded, control group by meeting their need for weight management. Follow-up occurs at 6 and 12 months.

Outcome measures include participant acceptability, measured qualitatively by semi-structured interviewing and quantitatively by recruitment and attrition rates. Feasibility of running the trial within primary care is measured by interview and questionnaire of the treatment providers. Adherence to the VLCD is verified by the presence of urinary ketones measured weekly. Daily urges to smoke, hunger and withdrawal are measured using the Mood and Physical Symptoms Scale-Combined (MPSS-C) and a Hunger Craving Score (HCS). 24 hour, 7 day point prevalence and 4-week prolonged abstinence (Russell Standard) is confirmed by CO < 10 ppm. Weight, waist and hip circumference and percentage body fat are measured at each visit.

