#### Inclusion Criteria

• Aged over 18 years

• Daily cigarette smoker with an exhaled CO of at least 10 ppm at least 15 minutes after last smoking

• BMI of at least 25 kg/m^2^

• Willing to be randomised to any of the three arms and willing and able to comply with the intervention and all study procedures

We are recruiting only those with a BMI greater than or equal to 25 for the following reasons: 1) The rate of weight loss on a VLCD is approximately 2 kg/week so anyone entering the trial would need to be able to lose 10 kg. For example, a woman 1.64 m tall weighing 68 kg with a BMI of 25.2 could potentially lose 10 kg and reach a healthy BMI of 21.6 kg/m^2^. VLCDs have been shown to be as safe in those with a BMI > 25 kg/m^2 ^as in those with a BMI > 30 kg/m^2 ^[18]. 2) Research shows that those who are overweight or obese are likely to gain more weight than healthy weight smokers and so they are an appropriate target for weight gain prevention [19]. 3) The smoking population has a lower mean BMI than the non-smoking population so we could potentially struggle to recruit only those with a BMI >30 kg/m^2^.

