##### VLCD

The VLCD formula Lipotrim is provided for the study at cost price from Howard Foundation Research Ltd. It is purchased by participating Primary Care Trusts (PCTs) and provided free to participants. Participants take 2-3 shakes each day and drink a minimum of 4 pints of water, but not in excess of 4 litres. Black tea and black coffee may be drunk but no other food or drink can be consumed as any additional carbohydrate or citric acid may suppress ketone production. The female formula totals 425 kcal and the male formula totals 559 kcal, it contains all essential nutrients and complies with the EU codex standard for VLCDs [16]. This diet is begun 1 week before quitting, by which time the dieter should be in ketosis. They continue this diet during the first 4 weeks after quitting when nicotine withdrawal symptoms are at their worst. The rationale for this is that they will be comfortably in ketosis when they quit and when in acute nicotine withdrawal.

Every effort is made to get the participant to adhere to the VLCD by using behavioural change techniques as defined by Abraham and Michie [22]. These include an explanation of the role of ketones and the necessity for strict adherence in order to remain in a ketotic state. (Providing instruction and providing information on consequences of action are behavioural change techniques 2 and 8.) Ketosis is usually achieved by the third or fourth day on the diet and so participants are advised that they will feel better after this time. Encouragement (technique 6) and prompting of self-encouragement (technique 22) is used e.g. 'today was difficult but if I keep going I will feel better in 2 days', 'if I can stick this out, I can lose weight and stop smoking in time for my birthday'. Support to identify and overcome barriers to adherence (technique 5) is also given.

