We have decided to advise an approximate energy deficit of 600 kcal. This is recommended by NICE for weight loss of 0.5 kg/week [16]. This is sufficient to counter the mean rate of post-cessation weight gain and promote modest weight loss which is desirable for our population with a BMI > 25 kg/m^2^. Dietetic consensus considers a usual maximum energy prescription of 1800 kcal. Anecdotally advising above this appears to be ineffective at achieving weight loss, this may be due to a people misunderstanding the volumes of food recommended for larger portion sizes.

To calculate energy prescription in individuals we have assumed all participants will have a physical activity level (PAL) of 1.4, which is consistent with a sedentary occupation and leisure activities. The PAL is the factor by which BMR is multiplied to give an estimate of total energy expenditure. For simplicity in clinical practice we have written dietary plans that equate to energy intakes of 1200 kcal, 1500 kcal or 1800 kcal. An individual is allocated the closest energy prescription to their BMR (as calculated by the Tanita body composition analyser). Calculating total energy requirement from a PAL of 1.4 and BMRs of 1200 kcal, 1500 kcal and 1800 kcal, shows energy requirement is an increase of 500 kcal-700 kcal above BMR. This means we can approximately achieve the 600 kcal deficit by using BMR alone for the prescription of energy. The energy level advised is translated into the appropriate number of portions from each of the food groups: complex carbohydrates, fruit and vegetables, meat, fish and alternatives, dairy foods, sugar and fatty foods. The proportion of food coming from these food groups make up a healthy diet with 15-30% of energy from fat, 10-15% of energy from protein, 55-75% of energy from carbohydrate and 0-5% energy from alcohol. Therefore the diet is low in fat and alcohol, two things that studies have shown significantly increase in the diets of smokers when they quit [26-28]. The dietary plan is a 'pick and choose' format, where individuals choose from a list of items within different food groups at each meal. The food portions are defined in American cup sizes and participants are given measuring cups to measure out their portions.

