#### VLCDs

Very low calorie diets are a recognised treatment for obesity. They form part of the NICE (2006) guidelines [14] for the management of adult obesity and are advised for up to three months of continuous use in people with a BMI > 30. We are using it for 5 weeks only in people with a BMI > 25. Weekly monitoring of weight means that if BMI falls below a healthy level treatment will be discontinued. VLCDs have been used safely for many years including in people with a BMI between 25 and 30 [16]. Since 1987 they have been subject to the regulations of the Committee on Medical Aspects of Food [39]. This is an extensively researched evidence based document detailing the formulation of VLCDs to ensure safety. The product to be used in this study complies with these standards. Thus, there is every reason to expect that treatment in this trial is safe.

Participants are warned about the side-effects of VLCDs and may contact the trial team to discuss any concerns. To this end, all participants are given a card the size of a credit card with the trial team's contact details on that will allow participants to receive advice on the VLCD or to report perceived serious adverse effects and receive advice as required. They are asked to carry this card with them at all times so that it can be used to notify medical personnel of a participant's treatment and trial involvement in case of emergency. Participants will record the occurrence of side-effects of VLCDs as specified by completing a checklist. The checklist is given to the trial healthcare professional and the healthcare professional will enquire about recorded adverse events, so as to determine the severity of any adverse event and ensure that appropriate advice is given for its management (e.g. drinking appropriate amounts of water to treat symptoms of mild dehydration.) Minor adverse reactions are monitored and managed in this way. For each known side effect listed in the checklist, the trial healthcare professional will have a definition of clinical severity. Any side effect that is classified as moderate or severe is reported to and discussed with the principal investigator. A decision on stopping therapy will then be made with the participant, attending clinician, principal investigator and other relevant parties as appropriate.

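### The VLCD adherence rule uses an approximate 2 kg weekly loss as a criterion, which conflicts with the ketone check in the abstract and can misstate the adherence rate

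*Protocol article*

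**What the plan says.** The Protocol article defines VLCD adherence in two places, differently.

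- Abstract, Methods: "Adherence to the VLCD is verified by the presence of urinary ketones measured weekly". No weight criterion appears.
- Measurement of diet and activity: "Those on a VLCD who do not produce ketones or achieve the expected 2 kg weekly weight loss will be considered non adherent". The sentence does not say whether missing one criterion is enough or both must be missed. Nor does it say whether 2 kg applies to each week or to an average over the diet.

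The source of the 2 kg is the justification of the BMI threshold under Inclusion Criteria: "The rate of weight loss on a VLCD is approximately 2 kg/week". There it is an approximate rate, used to argue that an entrant needs room to lose 10 kg.

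The label feeds a listed result. Among the quantitative acceptability measures is "Rates of participant adherence to treatment", and acceptability to participants is part of the primary objective.

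**The concern.** An expected rate describes a typical participant. Used as a pass mark, it also fails people who follow the diet fully but lose weight more slowly than the typical participant. If the article's energy figures do not support 2 kg of sustained weekly loss, the pass mark sits above what full adherence delivers for many of them.

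Weight change is also a trial outcome. If weight loss is part of the definition of adherence, those classed as adherent lose weight partly by construction.

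At stake is how the trial describes adherence to the VLCD. The article says its results will inform a larger trial, so a rate driven by the definition rather than by behaviour would be a poor guide.

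**Working it through.** **Inputs from the article**

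- Formula energy (VLCD section): "The female formula totals 425 kcal and the male formula totals 559 kcal". The abstract's range starts at 429; 4 kcal/day changes weekly loss by 4 × 7 / 8400 = 0.003 kg, so this does not matter here.
- Total expenditure is 1.4 × BMR, with worked BMR levels of 1200, 1500 and 1800 kcal (IDAP section).
- Conversion (IDAP section): of a deficit of about 600 kcal/day the article says "This is recommended by NICE for weight loss of 0.5 kg/week". This gives 600 × 7 / 0.5 = 8400 kcal per kg.
- Duration (safety section on VLCDs): "We are using it for 5 weeks only in people with a BMI > 25".
- Water: the Stage 2 VLCD section puts the body-water gain on re-feeding at up to 5 kg.

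**What reproduces.** 2 kg × 5 weeks = 10 kg, as under Inclusion Criteria. Expenditure above BMR is 0.4 × 1200, 1500, 1800 = 480, 600, 720 kcal, in line with the stated 500 to 700.

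**What does not: 2 kg/week.** Daily deficit = 1.4 × BMR − formula kcal. Weekly loss = deficit × 7 / 8400. Five-week loss = deficit × 35 / 8400.

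| Formula | BMR | Deficit (kcal/day) | kg/week at 8400 kcal/kg | kg/week at 7700 (assumed) | Five-week loss (kg) | Shortfall from 10 kg |
|---|---|---|---|---|---|---|
| 425 | 1200 | 1255 | 1.05 | 1.14 | 5.23 | 4.77 |
| 425 | 1500 | 1675 | 1.40 | 1.52 | 6.98 | 3.02 |
| 425 | 1800 | 2095 | 1.75 | 1.90 | 8.73 | 1.27 |
| 559 | 1200 | 1121 | 0.93 | 1.02 | 4.67 | 5.33 |
| 559 | 1500 | 1541 | 1.28 | 1.40 | 6.42 | 3.58 |
| 559 | 1800 | 1961 | 1.63 | 1.78 | 8.17 | 1.83 |

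A sustained 2 kg/week needs a deficit of 2 × 8400 / 7 = 2400 kcal/day. That is a BMR of (2400 + 425) / 1.4 = 2018 or (2400 + 559) / 1.4 = 2114 kcal.

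**Sensitivity to the conversion.** The kcal/kg at which a case just reaches 2 kg is deficit × 7 / 2. For BMR 1800 this is 7332 at 425 kcal and 6864 at 559 kcal. At an assumed 7000 kcal/kg, only BMR 1800 with 425 kcal passes (2.10 kg/week).

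**The two readings of the rule against the abstract**

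- *Missing either criterion fails.* A ketone-positive participant losing 1.8 kg in a week is adherent by the abstract and non-adherent by the rule. If 2 kg were the centre of a symmetric spread (assumption), about half of full adherers would fall below it in any one week.
- *Only missing both fails.* A ketone-negative participant losing 2 kg is adherent by the rule but not verified by the abstract. This also sits badly with the VLCD section, which makes strict adherence a condition of staying in ketosis.

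**If 2 kg is a five-week average.** The last column is the water loss needed. If the full 5 kg shift ran in reverse at the start of the diet (assumption), BMR 1200 on 425 kcal would average (5.23 + 5) / 5 = 2.05 kg/week and BMR 1800 on 559 kcal (8.17 + 5) / 5 = 2.63. An average of 2 kg is thus attainable, but smaller participants need nearly all of a shift that the article states as a maximum.

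**The case against.** The strongest reply is that the sentence need not be read harshly. In ordinary English, failing to do A or B often means doing neither, and on that reading no ketone-positive participant is mislabelled. The 2 kg may also be meant as an average, which early water loss could bring within reach. Both points stand. They remove the certainty of a downward bias, but not the conflict with the abstract or the lack of a stated rule.

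The abstract is a summary, and naming ketones as the check does not strictly exclude a second criterion. That is fair, but the body then adds one that can overrule the ketone result in one direction or the other.

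A reader might go further and infer any of the following, which the document does not support:

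- *Most adherent participants would be labelled non-adherent, or only about 3% would pass* (0.5 to the power 5). This needs the either-criterion reading, week-by-week judging, a median of exactly 2 kg and independent weeks. The article gives no distribution of BMR or weekly loss.
- *No participant could sustain 2 kg.* The 1800 kcal level is the top diet sheet in the IDAP arm, not a ceiling on BMR. Participants above about 2018 to 2114 kcal are not excluded. The 8400 kcal/kg also comes from a rounded pairing for modest restriction.
- *The decision on a larger trial rests on this rate.* The article states no progression criterion based on adherence; the rate is one of several descriptive items.
- *The ketosis analysis would lose ketone-positive participants.* The planned model includes everyone still trying to quit and tests ketosis itself as a mediator. It uses no adherence label.
- *IDAP adherence is also classified by weight.* That sentence states an expectation, not a rule.

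**Conclusion.** The point holds as a flaw in the definition of a descriptive measure. The article turns an approximate expected rate into an adherence criterion, and either reading of the rule can contradict the ketone check. Its own energy figures give 0.93 to 1.75 kg/week of sustained loss under full adherence at BMR 1200 to 1800 (1.02 to 1.90 at an assumed 7700 kcal/kg). Many adherent participants would therefore fall short once early water loss is over, and more often the smaller they are.

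The bias in the adherence rate is downward if missing either criterion counts and weeks are judged singly. If only missing both counts, the error runs the other way, by accepting ketone-negative participants. The size of the misclassification cannot be computed from the document. The conclusion rests on an activity factor of 1.4 and on a conversion near 7700 to 8400 kcal/kg. The sample size, the comparison of urges to smoke and the mediation analysis are untouched.

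**What to change.** Reconcile the abstract and the section on measuring diet and activity. For reporting, define VLCD adherence as the presence of urinary ketones at the scheduled on-diet visits (weeks 0 to +4), drop the 2 kg condition from the classification, and report weight change separately as an outcome. Stating only the time window and how the two criteria combine would remove the ambiguity, but would leave an approximate rate serving as a cut-off.

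This is a one-sentence change. It concerns classification only and alters no treatment, and ketones and weight are already recorded weekly. The price is that a dipstick gives a yes/no result once a week, so it cannot grade adherence and may miss lapses between visits. The IDAP sentence needs no change.
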